## Abstract

**Background:**

In coronary artery bypass grafting surgery, arterial conduits are preferred because of more favourable long-term patency and outcome. Anyway *the greater saphenous vein *continues to be the most commonly used bypass conduit. *Minimally invasive endoscopic saphenous vein harvesting *is increasingly being investigated in order to reduce the morbidity associated with conventional open vein harvesting, includes postoperative leg wound complications, pain and patient satisfaction. However, to date the short and the long-term benefits of the endoscopic technique remain controversial. This study provides an interesting opportunity to address this gap in the literature.

**Methods/Design:**

**Endoscopic Saphenous harvesting with an Open CO_2 _System **trial includes two parallel vein harvesting arms in coronary artery bypass grafting surgery. It is an interventional, single centre, prospective, randomized, safety/efficacy, cost/effectiveness study, in adult patients with elective planned and first isolated coronary artery disease. A simple size of 100 patients for each arm will be required to achieve 80% statistical power, with a significant level of 0.05, for detecting most of the formulated hypotheses. A six-weeks leg wound complications rate was assumed to be 20% in the conventional arm and less of 4% in the endoscopic arm. Previously quoted studies suggest a first-year vein-graft failure rate of about 20% with an annual occlusion rate of 1% to 2% in the first six years, with practically no difference between the endoscopic and conventional approaches. Similarly, the results on event-free survival rates for the two arms have barely a 2-3% gap. Assuming a 10% drop-out rate and a 5% cross-over rate, the goal is to enrol 230 patients from a single Italian cardiac surgery centre.

**Discussion:**

The goal of this prospective randomized trial is to compare and to test improvement in wound healing, quality of life, safety/efficacy, cost-effectiveness, short and long-term outcomes and vein-graft patency after endoscopic open CO_2 _harvesting system versus conventional vein harvesting.

The expected results are of high clinical relevance and will show the safety/efficacy or non-inferiority of one treatment approach in terms of vein harvesting for coronary artery bypass grafting surgery.

**Trial registration:**

www.clinicalTrials.gov NCT01121341.

## Background

Since the introduction of saphenous vein grafting by René Favaloro in the 1968, coronary artery bypass grafting (CABG) surgery has become one of the most common surgical procedures performed [1]. Although approximately 15% to 20% of vein grafts occlude in the first year with an annual occlusion rate of 1% to 2% in the first six years and 4% to 5% from 6 to 10 years, the greater saphenous vein continues to be the most commonly used bypass conduit [2].

Minimally invasive endoscopic saphenous vein harvesting was introduced by Lumsden in 1995 [3,4]. Ever since it has been increasingly investigated in order to reduce the morbidity associated with conventional open vein harvesting, which requires long incisions, and thus postoperative leg wound complications, pain and patient dissatisfaction [5-7].

Data from the Society of Thoracic Surgery National Database (accessed at http://www.sts.org) show that in 2008 endoscopic harvesting was used in approximately 70% of CABG surgeries performed in USA, while in Europe its use is for various reasons still limited.

In 2005, the International Society for Minimally Invasive Cardiothoracic Surgery published a consensus statement on the use of endoscopic vein harvesting (EVH) versus open vein harvesting (CVH) in CABG aimed to determine which resulted in better clinical and resource outcomes [8]. The members of the consensus committee concluded that EVH was recommended to reduce leg wound related complications, decrease postoperative pain, accelerate postoperative mobility, improve patient satisfaction, reduce length of stay in the hospital, and use of outpatient wound-management resources; as to the quality of the conduit harvested, major adverse cardiac events (MACE) and angiographic patency at 6 months, EVH and CVH techniques were judged to fare equally.

As now, the evidence for short-term patient benefits in reducing infections and operative complications while improving patient mobility and satisfaction is sufficiently replete, including the conclusion that wound complication management following EVH requires significantly less resource utilization than for CVH and thus increase its cost-effectiveness [9].

The mid- and long-term outcome are instead still controversial issues. This may be partly due to the fact that the event-free survival rate over periods from 2 to 5 years is commonly taken as a surrogate marker for graft failure, since postoperative angiographic studies, the gold standard to evaluate the long-term influence of vein harvest technique on graft patency, are not widely used owing to their low practicality and high costs.

A recent pooled meta-analysis of all observational and randomized trials of short- to midterm follow-ups shows no differences in survival [10]. Allen et al. [11] quote as outcome of their 112 prospectively randomized patients a freedom from MACE at five years of 75% for EVH vs. 74% for CVH, which leads them to conclude that the use of endoscopic versus traditionally harvested saphenous vein does not influence event-free survival. A different opinion is instead voiced by Lopes et al. [12] who carry out a single retrospective post hoc analysis of the PREVENT IV trial, and, based on the event-free survival rates at three years of 80% for EVH vs. 83% for CVH, conclude that EVH may have a negative impact on graft patency. Actually, the relatively small gap between the event-free survival rates for the two approaches (1-3%) would require enormously large sample sizes to be established with a statistical power of at least 80%.

The comparison and discussion of EVH vs. CVH results often neglects to consider the impact of the use of endoscopic devices for vein harvesting which differ both for dissection technique and usage of CO_2. _Cheng et al. [13] underline that the Lopes' conclusions on the PREVENT IV trial may have been influenced by the fact that large part of the analysed EVH cases were performed with a closed CO_2 _system device (GUIDANT) which has a documented tendency to form clots within the vein, if heparin is not given before dissection (as it was actually the case at the times of that trial). They add other indications of device-related different outcomes: a long-term randomised controlled trial (RCT) carried out with a Ethicon (now Sorin) device showed in a 5-year follow-up no difference in MACE, while two others RCTs and a subset data of the PAS-Port proximal anastomosis system trial using Guidant (now Maquet) showed non-significant trends in worse vein-graft patency following EVH.

The device used and all the related technicalities with the ongoing improvements over the years may well be the divide among different evaluations. As a consequence, great care must be used when comparing results from trials carried out several years apart from each other.

These considerations formed the rationale for our Endoscopic Saphenous harvesting with an Open CO_2 _System (ESOS) Trial, whose protocol is herein illustrated.

## Methods/Design

The study site for this trial is the Department of Thoracic Surgery, Division of Cardiac Surgery of San Giovanni Battista Hospital-University of Turin, Italy. This center has a long-term well-established familiarity with minimally invasive techniques; from here stems the decision to extend to CABG the practice to endoscopic saphenous vein harvesting, in order to improve clinical outcomes and provide major benefits to patients.

To acquire a specific expertise in EVH with the device chosen, in the first half of 2010, prior to trial patient recruitment, there has been a 6-months break-in period dedicated to satisfactorily complete all aspects of the learning curve. 20 patients scheduled to have coronary artery bypass grafting judged amenable to the endoscopic approach were enrolled. This number is consistent with what reported by authors who went through the same learning curve process [14-16].

All results obtained in this period concur to state that the mastery of the vein harvesting technique has been successfully achieved [17,18]. The total procedure time and the number of incisions have decreased, while the vein harvest rate, or length-time index has consistently increased to reach the value of 1 cm/min suggested by Crouch et al. [19] as optimal for this method (95% CI: 0.89-1.04). Other important results have been low incidence of wound-related morbidities, absence of infection, no need for hospital re-entry or ambulatory medications after discharge, general satisfaction expressed by all patients for the prompt wound healing, the good mobility, the absence of pain and the presence of a very small scar, due to become soon scarcely discernible.

In order to ensure that during the trial all vein harvesting procedures with all their technicalities will be carried through uniformly, and thus avoid a further stratification, the vein harvesting is planned to be performed by a single surgeon ([name]). Should other surgeons be enrolled, a careful evaluation of homogeneity of results from the different operators will be mandatory.

### Ethics and Trials Registration

The study is funded by a 2010 grant from the Azienda Ospedaliera-Universitaria San Giovanni Battista of Turin. The trial has been approved by the local Ethic Committee and registered at the United States National Institutes of Health Clinical Trials Registry (ClinicalTrials.gov ID ***NCT01121341***), available online at http://www.clinicaltrials.gov.

### Primary end points

We have two primary end points (see Appendix 1) with different deadlines:

• a short-term one (6 weeks after CABG surgery), regarding freedom from wound complications, defined as cellulitis, edema, ecchymosis, hematoma, cellulites, drainage, necrosis, dehiscence, debridement; leg wound infection according to ASEPSIS score;

• a long-term one (2 years after CABG surgery), regarding freedom from MACE, i.e. death, myocardial infarction, recurrent angina or congestive heart failure due to vein graft failure with assessment of vein-graft patency.

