In the course of the trial all consecutive adult patients (18 years and older) with elective planned and first isolated coronary artery disease (CAD) amenable to coronary artery bypass grafting surgery will be screened to establish their eligibility to both EVH and CVH on the basis of the guidelines reported in Table 1.

Patients not amenable for both treatment options, or who are expected to have a better outcome with one of the two, will not be included in the trial; neither will be the patients who refuse to be randomized because of their personal preference for one approach over the other.

Patients deemed amenable for both harvesting modalities, after having signed the informed consent, will be assigned by means of a standard web-based computer generated randomization scheme to one of the two cohorts, either EVH or CVH, and after allocation they will be included in the intention to treat analysis. An independent clinical research assistant will be responsible for randomization and treatment assignment.

The post surgery follow-up will consist of clinic visits on the sixth week after CABG surgery and at occurrence of any adverse event. Each information leading to in-patient or out-patient treatment regarding major adverse cardiac events, vein-graft failure or occlusion or other morbidity, will be collected. The number of visits required to clear up each wound complication will be used as a surrogate to determine outpatient resource utilization for wound management.

Follow-up angiograms will be performed at 18 months to explore directly vein graft longevity. This will allow not to rely totally on the indirect, and sometimes deceiving, information supplied by the event-free survival rates.

Follow-up will stretch over a minimum of 24 months. At the end of this period there will be an assessment of the state of the art based on the results obtained with the two different approaches, whose rationale will lead to the decision to either conclude or continue the follow-up.

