**Figure 1 F1:**
[figure not shown]
**Flowchart of the study design**. This figure illustrates the study design.

All data relative to enrolled patients will be entered in a database containing preoperative demographics and risk factors (age, sex, BMI, morbidities, coronary artery lesions severity by SYNTAX score and surgical risk profile by EUROscore, etc), intra-operative variables (site of harvesting, number of incisions, lengths, times, etc), vein specific variables, pre- and post- harvesting respiratory and hemodynamic parameters, histological status of the harvested vein, as examined and graded by a pathologist. Wound healing and variables in the ASEPSIS score and other wound-related morbidities, wound complications, outcome and correlated events of the follow-up are to be evaluated by an independent clinical committee every 6 weeks in the first year, and then at 18 and 24 months. The total number of data characterizing each patient will be approximately 180, a complete scenario of his risk factors, surgical and post surgery history, short-, mid- and long-term outcome. The two cohorts will hence be described by two 115 × 180 arrays, with the intention to bring to light differences and similarities in behaviors and trends by means of a thorough statistical analysis.

The continuous data will be reported as average ± standard deviation and will be analyzed by standard ANOVA tests. Discrete or dichotomous values will be reported as percentages, risk ratios (and their 95% confidence intervals), and will be stratified in *mxn *contingency tables, analyzed for significant differences by chi-square tests (with Yates'correction in the case of 2 × 2 tables) and Fisher or mid-P tests.

The freedom from late wound complications and in general all event-free survival rates will be obtained according to the Kaplan-Meyer method, with the statistical differences among them estimated by the Mantel-Cox log-rank test. As usual, statistical significance will be determined at a *p *value (probability of null hypothesis: the observed differences are imputable to chance) ≤ 0.05, corresponding to the false positive probability (α or type I error). In case of a *p *value > 0.05, the next step will be the estimate of the test power *II *and the related false negative probability (β or type II error = 1- *II*).

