## Discussion

Nowadays, a research to evidence benefits, harms and resource implications of EVH vs. OVH must not only meet the requirements of being prospective, randomized and including a great number of baseline, inter-operative, post-operative and follow-up co-founding variables, but needs also to exploit the latest improvements in the available technologies of vein harvesting.

The Endoscopic Saphenous harvesting with an Open CO_2 _System (ESOS) Trial, was configured after these guidelines.

Its primary goal is to compare and to quantify improvements in short and mid-term outcomes after endoscopic open CO_2 _harvesting (EVH) versus conventional open vein harvesting (CVH): safety/efficacy, leg wound infections and morbidity, patient satisfaction, short and long-term outcome, with histological and angiographic studies will be matter of thorough investigation.

The results on wound healing, mobility, patient satisfaction, health-related quality of life, safety/efficacy, cost-effectiveness are expected to be available shortly after the beginning of the trial. The mid-term outcomes and vein-graft patency will be estimated at the end of the 2-year follow-up, when a possible extension of the period of observation will also be considered.

A secondary goal of ESOS is to provide guidance to physicians on optimal CABG strategies for patients with different risk levels. A more widely spread and accurate knowledge on this issue may also help patients in their choices in a difficult predicament of their life when they have to take fundamental decisions for their health.

When compared to CVH procedure, EVH is expected to confer a 16% reduction in leg wound infections. If the use of new improved instrumentation will also improve the long-term event-free survival rate, as we hope, endoscopic saphenous vein harvesting should then be definitely recommended to patients with CAD, also for the high level of satisfaction usually reported by patients undergoing this minimally invasive procedure.

This study, besides providing new information aimed to improve the quality of care for CAD patients, will also assess the cost/effectiveness of this approach as far as in-patient and out-patient care is concerned.

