## List of abbreviations used

ESOS: Endoscopic saphenous harvesting with an open CO_2 _system; CABG: Coronary artery bypass grafting; CAD: Coronary artery disease; PCI: Percutaneous coronary intervention; EVH: Endoscopic vein with open CO_2 _harvesting; CVH: Conventional vein harvesting; SV: Saphenous vein; MACE: Major adverse cardiovascular events: death; myocardial infarction; revascularization (PCI or CABG) for ischemia or angina recurrence; GF: vein-graft failure at least 75% of stenosis at angiographic study; GO: vein-graft occlusion

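### The 2-year primary end point, freedom from MACE, has two incompatible definitions, and the follow-up that would detect its events is described in two ways that need reconciling

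*Protocol article*

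**What the plan says.** The protocol article has two primary end points. The second is "a long-term one (2 years after CABG surgery), regarding freedom from MACE", which the Primary end points section spells out as "death, myocardial infarction, recurrent angina or congestive heart failure due to vein graft failure with assessment of vein-graft patency". The List of abbreviations used expands the same acronym as "Major adverse cardiovascular events: death; myocardial infarction; revascularization (PCI or CABG) for ischemia or angina recurrence". That list also defines vein-graft failure by angiography, as a stenosis of 75% or more. Under Trial Population, and Statistical Analysis, event-free survival is to be estimated by Kaplan-Meier and compared by the log-rank test.

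On follow-up, the text closing the Secondary end points section states: "The post surgery follow-up will consist of clinic visits on the sixth week after CABG surgery and at occurrence of any adverse event". It adds that follow-up lasts at least 24 months. The text after Figure 1, under Trial Population, and Statistical Analysis, says that wound outcomes and follow-up events "are to be evaluated by an independent clinical committee every 6 weeks in the first year, and then at 18 and 24 months".

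On patency, the Secondary end points section says "Follow-up angiograms will be performed at 18 months to explore directly vein graft longevity". The Discussion says "The mid-term outcomes and vein-graft patency will be estimated at the end of the 2-year follow-up".

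**The concern.** A composite primary end point needs one list of components. Here the two lists share only death and myocardial infarction without dispute, and even those are uncertain if the graft-failure condition reaches them. A time-to-event analysis needs a single rule for when a patient has had the event, and the article prints two. Whoever analyses the trial would have to choose between them, possibly after data have accrued, and the reader could not tell which choice had been planned.

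Detection of events is a second, softer problem. One section fixes no clinic visit after week 6 unless something happens. Another expects evaluations up to month 24. If contact is mainly event-driven, its frequency could differ between arms, because the protocol itself expects wound complications in about 20% of the conventional arm and under 4% of the endoscopic arm. The documents do not show that this would happen, but one common schedule would rule it out.

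**Working it through.** No formula decides this point. The two definitions are set side by side for typical patients.

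| Patient within 2 years | Primary end points | List of abbreviations used |
|---|---|---|
| Dies, no angiogram | Event if the graft condition does not reach death; otherwise cannot be classified | Event |
| Infarction, graft status unknown | Same uncertainty | Event |
| Recurrent angina, no procedure | Event, subject to the graft condition | Not an event on the natural reading |
| Congestive heart failure | Event, subject to the graft condition | Not an event |
| Revascularized for ischemia without angina | Not an event | Event |
| Revascularized for recurrent angina | Event through the angina, subject to the graft condition | Event |

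**Scope of the condition.** It stands at the end of the series, so it can be read as covering every component, angina and heart failure only, or heart failure only. If it covers every component, the protocol's own criterion for graft failure requires angiography. A death without one then cannot be classified, and events after month 18 have no scheduled angiogram to support attribution.

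**Follow-up.** Fixed contacts in the Secondary end points text are the week-6 visit and the 18-month angiogram; all other visits are event-driven. The text after Figure 1 requires evaluations every 6 weeks in year 1 and at months 18 and 24. No scheduled clinic visit is named to feed the 24-month evaluation.

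**The plan's own long-term figure.** The article says at least 3000 per cohort would be needed for 80% power with a difference or margin of 2 to 3 points. Sidedness is not stated; two-sided 0.05 is assumed. For event-free rates of 80% and 77%:

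n = [1.96·√(2·0.785·0.215) + 0.842·√(0.80·0.20 + 0.77·0.23)]² / 0.03² = 2943 per arm, or 3009 with continuity correction.

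The figure therefore reproduces at the 3-point end.

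**What a change of definition could do.** No event rate is given under either list, so the rates e below are assumptions. At 100 per arm, the 95% half-width for the difference between arms is 1.96·√(2e(1−e)/100). The number per arm for a 3-point margin (one-sided 0.025, 80% power) is 7.849·2e(1−e)/0.03².

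| Assumed event rate | Half-width, points | n per arm |
|---|---|---|
| 10% | 8.3 | 1570 |
| 20% | 11.1 | 2791 |
| 25% | 12.0 | 3271 |

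The definition changes which events are counted and how precise the comparison is. It does not change recruitment: the article sets 115 per cohort as a balance of statistical requirements and resource limits, and accepts that the long-term comparison would need far more.

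**The case against.** Several objections have force.

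- **Unseen documents.** The Primary end points section refers to Appendix 1, which is not shown and may give one definition; an analysis plan may too. That limits what can be said about the wider consequences. It does not remove the conflict between two printed definitions.
- **Clinic visits and committee evaluations are different things.** They can coexist, and an article may leave the contact schedule to the full protocol. This largely stands and makes the follow-up point a matter of reconciliation. Still, the Secondary end points text says what follow-up consists of and names no clinic visit that would supply the later evaluations.
- **Patency.** Images taken at 18 months can be reported at the end of 2 years. This stands: there is no contradiction, only a need to label the time point.
- **The comparison is imprecise anyway.** True under either list, but a primary end point still needs one meaning.

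A reader might also infer more than the documents support:

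- **A numerical gap to set against the 2-3% margin.** Suppose the components unique to each list add x and y points, each assumed to be 2 to 5. The event rates then differ by |x − y|, which is 0 to 3 points; the two amounts offset and do not add. The margin concerns the difference between arms, and a definition that shifts both arms alike leaves that difference unchanged.
- **Deaths will be censored.** Nothing says so. The scope of the condition is unclear, and information on graft failure is also collected when events occur.
- **Attribution is made with the arm known.** The article names an independent committee and does not say whether it is masked.
- **The 18-month angiogram creates MACE events.** Revascularization counts in the abbreviations list only when done for ischemia or angina recurrence, so an angiographic finding alone does not qualify as written.

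**Conclusion.** The definition of MACE is contradictory as printed and must be reconciled, because it is one of only two primary end points. The conclusion rests on the text alone: the two lists differ in heart failure, in revascularization, in angina without a procedure (on the natural reading) and in attribution to a graft. If the attribution condition covers all components, deaths without an angiogram cannot be classified by the article's own criterion. The effect on event rates or on the difference between arms cannot be computed from the document. The follow-up mismatch is real but softer, and the patency timing needs only a label.

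**What to change.** By protocol amendment, before outcome data are examined:

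1. Use one MACE list in both the Primary end points section and the List of abbreviations used, and in Appendix 1 if it differs.
2. Count death from any cause, and state which other components, if any, require attribution to vein graft failure.
3. Keep graft-attributed events as a secondary analysis.
4. Reconcile the visit text in the Secondary end points section with the evaluation schedule after Figure 1, so that one outcome-contact schedule applies to both arms through 24 months.
5. Label angiographic patency as an 18-month measure wherever it appears.

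The cost is mainly wording. The sample size does not change. If the evaluations already listed are taken as the schedule, any extra contacts are ones the article already implies. Recruitment was under way when the article appeared, so the amendment is cheapest if made early.
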